### Sample size calculation

On the assumption, based on published data, that the mean LVM/BSA of hemodialysis patients determined by cMRI is 100 g/m^2^ with a standard deviation of 25 g/m^2^ [42] and an expected treatment effect of delta LVMI of 20 g/m^2^, 25 patients are needed per group to detect this difference with 80% power using a two-sample *t* test at an alpha level of 0.05. Assuming 10% attrition (drop out/loss to follow-up) within 1 year of follow-up, the final sample size in the intention-to-treat analysis will be 31 patients.

Patients receiving a renal transplant as well as those who become pregnant (which is unlikely due to the significantly reduced fertility of women under dialysis) will drop out of the study.

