**Methods/design:**

This single-blinded randomized trial of 12 months duration will test the effects of ETL compared with alfacalcidol on LVH and cardiac fibrosis in maintenance hemodialysis patients with secondary hyperparathyroidism. Both treatment regimens will be titrated to equally suppress secondary hyperparathyroidism while alfacalcidol treatment causes an increase and ETL a decrease in FGF23, respectively.

Patients treated thrice weekly with hemodialysis for ≥ 3 months and ≤ 3 years with parathyroid hormone levels ≥ 300 pg/ml and LVH will be enrolled in the study.

The primary study endpoint is change from baseline to 12 months in left ventricular mass index (LVMI; g/m^2^) measured by cardiac magnetic resonance imaging. Sample size calculations showed that 62 randomized patients will be necessary to detect a difference in LVMI of at least 20 g/m^2^ between the two groups at 12 months. Due to the strong association of volume overload and LVH, randomization will be stratified by residual kidney function, and regular body composition monitoring will be performed to control the volume status of patients.

Study medication will be administered intravenously by the dialysis nurses after every hemodialysis session, thus omitting adherence issues.

Secondary study endpoints are cardiac parameters measured by echocardiography, biomarker concentrations of bone metabolism (FGF23, vitamin D, parathyroid hormone, calcium, phosphate, s-Klotho), cardiac markers (pro-brain natriuretic peptide, pre- and postdialysis troponin T) and metabolites of the renin–angiotensin–aldosterone cascade (angiotensin I (Ang I), Ang II, Ang-(1–7), Ang-(1–5), Ang-(1–9), and aldosterone).

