### Statistical methods

Data will be described as means and standard deviation or medians and interquartile range for continuous symmetric and skewed variables, respectively. Distributions of the analyzed parameters will be visualized by boxplots and histograms.

The primary endpoint (change in LVMI from baseline to 12 months) will be analyzed by the analysis of covariance. The main variable in the model to be tested will be treatment group, which represents the treatment effect on change in LVMI 1 year after baseline between the two treatments. Baseline LVMI for each patient will be used as a covariate in the model and the interaction between treatment group and baseline LVMI will be included. Furthermore, to account for stratification during randomization, the stratification factors will also be included in the model. The secondary endpoints (changes in FGF23, s-Klotho, PTH, 25(OH)D, 1,25(OH)_2_D, proBNP, pre- and postdialysis TnT and RAAS metabolites) will be analyzed analogously. All analyses will be conducted according to the intention-to-treat principle. Two-sided *p* values lower than 0.05 will indicate statistical significance.

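### The step from 25 to 31 patients per group does not follow from the stated 10% attrition, which gives 28 or 29 per group (56 to 58 in total), not 62

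*Protocol article*

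**What the plan says.** The Sample size calculation section takes a mean LVM/BSA of 100 g/m² "with a standard deviation of 25 g/m^2" and "an expected treatment effect of delta LVMI of 20 g/m^2". From these it concludes that "25 patients are needed per group to detect this difference with 80% power", naming a two-sample t test at alpha 0.05. The Statistical methods section makes the test two-sided: "Two-sided *p* values lower than 0.05 will indicate statistical significance".

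The next sentence adds the allowance for loss, "Assuming 10% attrition (drop out/loss to follow-up) within 1 year of follow-up", and ends with "the final sample size in the intention-to-treat analysis will be 31 patients". No group label is attached to the 31.

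The abstract reports that "62 randomized patients will be necessary to detect a difference in LVMI" of at least 20 g/m². The Study design section also gives 62 subjects, and the section on screening and randomization gives 1:1 allocation. The 31 is therefore a per-group figure. The sample size section mentions no allowance other than the 10%.

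**The concern.** The article prints every input and the result, and the last step does not connect them. Ten percent attrition on 25 per group leads to 28, not 31. This is not a detail left to a fuller document, because the figures shown disagree with each other.

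At stake is which attrition the design assumed. The Cardiac MRI section plans only two scans, at baseline and after 12 months, so a patient who leaves early will generally have no follow-up value for the primary endpoint. The sample size section counts transplant recipients as drop-outs, and the Discussion gives transplant waiting time and high mortality on dialysis as reasons for limiting follow-up to 12 months. Whether 10% or nearly 20% loss was planned for is a real design assumption, and a reader cannot recover it from the text.

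The missing label is a second, smaller fault. Read literally, the sentence gives 31 patients for the whole trial.

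**Working it through.** **Inputs.** From Sample size calculation: SD 25 g/m², difference 20 g/m², power 80%, alpha 0.05, two-sample t test, 25 per group, attrition 10%, final size 31. From Statistical methods: two-sided testing. From the abstract and Study design: 62 in total. From the randomization section: 1:1 allocation.

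**Step 1: reproduce the 25 per group.** The standardised difference is 20/25 = 0.8.

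- Normal approximation: n = 2 × (1.960 + 0.842)² × (25/20)² = 24.5, rounded up to 25. Power at 25 is 80.7%.
- Exact (noncentral) t test: power is 79.1% at 25 and 80.7% at 26, so 26 are needed for 80%.

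The stated 25 therefore reproduces by the usual formula and is one patient short by the exact one. The start of the calculation is sound.

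**Step 2: apply the stated 10% attrition.**

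| Start per group | Calculation | Per group | Total | Surplus in 62 |
|---|---|---|---|---|
| 25 | 25/(1 − 0.10) = 27.8 | 28 | 56 | 6 (6/56 = 10.7%) |
| 25 | 25 × 1.10 = 27.5 | 28 | 56 | 6 |
| 26 | 26/(1 − 0.10) = 28.9 | 29 | 58 | 4 (4/58 = 6.9%) |

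None of these gives 31 per group or 62 in total.

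**Step 3: what would give 31?**

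- Attrition implied by going from 31 to 25: 1 − 25/31 = 19.4%.
- Attrition implied by going from 31 to 26: 1 − 26/31 = 16.1%.
- A 20% loss: 25/0.80 = 31.25, which is 31 to the nearest whole patient and 32 if rounded up.
- Ten percent applied twice in sequence: 25/(0.9 × 0.9) = 25/0.81 = 30.9, rounded up to 31.

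The text states none of these.

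**Step 4: could the interim analysis explain the gap?** The Data Safety Monitoring Board section sets one early look with stopping at p < 0.000207, which uses almost no alpha. Suppose, as an assumption, that the look costs 1% in sample size: 25 × 1.01/0.9 = 28.06, still far from 31. The sample size section does not cite the interim look as a reason for more patients.

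**Step 5: what 62 randomised patients deliver (exact t test).**

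| Loss | Remaining per group | Power for 20 g/m² |
|---|---|---|
| 10% | 31 × 0.9 = 27.9, about 28 | 83.6% (normal approximation 84.9%) |
| about 19% | 25 | 79.1% (normal approximation 80.7%) |

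With 28 per group, the difference detectable with 80% power is 19.1 g/m². This is the same surplus expressed on the effect scale, not a second discrepancy.

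**The case against.** The strongest defence is that the error does no harm. Sixty-two patients are more than the stated inputs need, so under its own assumptions the trial is not made underpowered by this step. That stands, and it limits the weight of the point.

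A second defence is that the attrition sentence names two kinds of loss, drop-out and loss to follow-up. Ten percent for each, in sequence, gives 30.9 and so 31. This is a plausible account of how the number arose. However, the sentence gives one 10% figure covering both, so the account is a guess that only the sponsor can confirm. Deliberate over-recruitment is equally possible and equally unstated, and it sits badly with the abstract's claim that 62 are necessary.

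The intention-to-treat label is also partly defensible. An intention-to-treat set contains everyone randomised, so 31 per group can be its size, and the handling of patients without a 12-month scan may properly be left to the analysis plan. What remains is that the number randomised and the number on which the power rests should be kept apart, and that the group label is missing.

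A reader might go further and infer that the stated 80% power, or the 20 g/m² difference, is wrong. The documents do not support that. Both are tied to 25 per group, where they reproduce. No power is claimed for 31 per group, and the abstract gives no power figure. The abstract's threshold of at least 20 g/m² is also met with 62 patients at 10% loss. Nor do the documents show that 10% understates the expected loss; they show only that 10% does not lead to 31.

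**Conclusion.** The point holds as an arithmetic inconsistency confined to the attrition step. Under the stated inputs the number to randomise is 28 per group (56) from the plan's own 25, or 29 per group (58) from the exact t-test requirement of 26. The stated 31 per group (62) exceeds this by 4 to 6 patients and matches an unstated loss of about 16% to 19%, or 10% taken twice. Sixty-two are therefore not necessary under the inputs as written.

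The direction is conservative. Power for 20 g/m² is about 84% if 10% are lost and about 79% (exact) if about 19% are lost. These figures take the plan's SD of 25 g/m², its two-sample t test, and equal loss in both groups as given. The point should be fixed as a correction to a stated design figure. It does not call the trial's size into question.

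**What to change.** Keep 62 and reword the attrition sentence in one of two ways, according to what was actually assumed:

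- 31 patients per group randomised allows for about 19% attrition and leaves 25 per group, with about 79% power by the exact t test (about 80% by the normal approximation); or
- 31 patients per group randomised, with 10% attrition, leaves about 28 per group and about 84% power for 20 g/m².

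If 10% was meant separately for drop-out and for loss to follow-up, say so and show 25/0.81. In either form, write 31 patients per group randomised in place of 31 patients in the intention-to-treat analysis, and change the abstract so that its claim of necessity agrees with the chosen statement.

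The cost is one reworded paragraph and one abstract sentence. No patients, endpoints, tests or decision rules change.

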### Study registration

The study was approved by the Austrian regulatory authority (Federal Office for Safety in Health Care, Austrian Agency for Health and Food Safety, AGES reference number 10087746) and was registered in the European Clinical Trials database (EudraCT, 2017–000222-35) and in a public clinical trial database (ClinicalTrials.gov, NCT03182699).

## Discussion

In our proposed trial we will provide novel insights into the extent of FGF23-mediated cardiac remodeling in patients on chronic hemodialysis. We specifically hypothesize that treatment with ETL ameliorates pathological changes in the cardiac structure of dialysis patients with sHPT by suppression of systemic FGF23 levels.

The EVOLVE study investigated the effect of lowering FGF23 with the use of cinacalcet on cardiovascular mortality in 3883 hemodialysis patients with sHPT. They were able to show that a reduction in FGF23 of ≥ 30% after 20 weeks of therapy showed a trend towards a decrease in cardiovascular mortality, sudden cardiac death and heart failure [35, 57].

A small study conducted by Choi et al. described a significant reduction in LVMI and a significantly improved diastolic function, measured by echocardiography, in 12 hemodialysis patients treated with cinacalcet [58].

In our proposed trial we make use of the deviant influence of ETL versus ALFA on the serum levels of FGF23 since, as mentioned previously, calcimimetic drugs decrease FGF23 while vitamin D increases it. Consequently, we generated a human model to study the influence of changing serum FGF23 levels on cardiac structure using approved medication for sHPT. We established PTH target values of 100–300 pg/ml considering the Kidney Disease: Improving Global Outcomes guidelines in order to demonstrate the effect of FGF23 independent of PTH. Study medication will be provided intravenously, allowing a very consistent delivery of the drug. One of the most important advantages of the intravenous treatment is the elimination of possible noncompliance. Patient adherence to oral cinacalcet therapy is known to be very low [59]. Another major advantage of this study when comparing it to the trial by Choi et al. is the use of cMRI as the diagnostic tool for the quantification of left ventricular mass, lowering the inter- and intraobserver variability known from using echocardiography. cMRI provides accurate anatomic information that is in excellent agreement with autopsy results [60, 61]. It is also able to detect LVH in patients with seemingly normal echocardiographic results due to a geometric assumption-free quantification of left ventricular mass [62, 63].

Based on the strong association of volume overload with CKD progression and adverse cardiac outcome we will perform a stratified randomization procedure to ensure an equal distribution of dialysis patients with residual renal function (i.e., ≥ 500 ml urine/day) and those without (< 500 ml urine/day) in both treatment groups [64]. Additionally, only patients reaching their individual optimal dry weight will be allowed to participate in the study.

This trial is designed to treat patients with either study medication for 12 months. It can be argued that this amount of time is too short to reproduce a measurable change in cardiac structure. It is important to consider that it takes a certain amount of time to develop sHPT under dialysis and to reach a severity requiring intravenous treatment. Additionally, in Austria the median time spent on the waiting list for renal transplantation is around 3 years, not to mention the high mortality of patients under dialysis. Consequently, in order to avoid a high drop-out as well as out-of-feasibility reasons, we decided this precise follow-up time period.

The diagnosis of LVH prior to enrollment in the study poses a certain difficulty regarding the accuracy of echocardiographic quantification of LVH. However, since each patient serves as his or her own control, the progression of left ventricular mass can be demonstrated during the course of the 12 months of treatment.

This trial is designed to visualize changes in cardiac muscle mass and fibrosis as a result of modified FGF23 levels which might be causal to the improved cardiovascular outcomes under lower FGF23 described in the EVOLVE study. If our study proves that ETL can effectively ameliorate LVH and cardiac fibrosis trough a suppression of FGF23, it may potentially provide a valuable basis for a pharmaceutical target aiming at reducing the high rate of cardiac death in patients under maintenance hemodialysis.

## Trial status

This is Protocol version 1.0, 28 May 2019. Recruitment of study patients started in October 2017 and enrollment is estimated to be complete as of November 2019.

## Data Availability

The data that support the findings of this study will be available from the corresponding author upon reasonable request.

## Abbreviations

1,25(OH)_2_D: 1,25-Dihydroxyvitamin D
25(OH)D: 25-Hydroxyvitamin D
ACE: Angiotensin-converting enzyme
AE: Adverse event
ALFA: Alfacalcidol
Ang: Angiotensin
BCM: Body composition monitoring
BNP: Brain natriuretic peptide
CKD: Chronic kidney disease
cMRI: Cardiac magnetic resonance imaging
ETL: Etelcalcetide
FGF: Fibroblast growth factor
FGFR: Fibroblast growth factor receptor
LVH: Left ventricular hypertrophy
LVM/BSA: Left ventricular mass indexed for body surface area
LVMI: Left ventricular mass index
PTH: Parathyroid hormone
RAAS: Renin–angiotensin–aldosterone system
sHPT: Secondary hyperparathyroidism
SUSAR: Suspected unexpected serious adverse reaction
TnT: Troponin T
